**Study drugs:** The TZD that will be used is *pioglitazone hydrochloride*. Subjects in groups 3 and 4 will begin pioglitazone 15 mg orally every day for 8 weeks total. During weeks 9-12, subjects who have tolerated 15 mg pioglitazone daily will be increased to 30 mg/day and will remain at this dose for the duration of the study. However, the pioglitazone dose may be decreased or, in rare circumstances, increased if side effects such as peripheral edema or diabetes develop (please see *Pages 13 and 14* for TZD dose adjustments). Pioglitazone has been prospectively shown to reduce visceral fat content and improve insulin sensitivity in insulin resistant people. It is begun 4 weeks prior to rhGH in order to allow sufficient time for its insulin sensitizing effect to occur. RhGH-treated subjects will begin self-injecting rhGH 8 mcg/kg SQ every day at week 5 and will continue to do so for the duration of the study, unless side effects develop (please see *Pages 13 and 14* for rhGH dose adjustments). The total rhGH treatment period will be 9 months. Previous studies have indicated that this dosage and duration of treatment are generally well tolerated and effective in significantly reducing visceral fat.

**Diet, exercise and activity:** Subjects will adhere to their usual daily dietary consumption and exercise routine for the duration of the study. They will be asked to report any significant changes in dietary intake or physical activity.

**Physical exam:** A complete physical exam will be performed at baseline (week ­- 4 to 0) and again at weeks 4, 8, 12, 16, 20, 24, 32, 40 and 43. In addition, supine systolic and diastolic blood pressure will be measured in mmHg using a manual sphygmomanometer.

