**Insulin Sensitivity Test (IST):** Endogenous insulin sensitivity will be measured using a 3-hr insulin sensitivity test (33,34). This test will be performed at baseline and again at week 43 (which follows a 3-week washout period for study medications). An intravenous catheter will be placed into each antecubital vein. One catheter will be used for blood draws for glucose measurements and the catheter in the contralateral arm will be used for infusion of octreotide, insulin and 20% dextrose. The 3 infused substances will be administered simultaneously. Octreotide acetate will be used to suppress endogenous secretion of insulin and will be infused at 0.27 µg/m2 per minute. Insulin will be infused at 32 mU/m2·min and glucose will be infused at 267 mg/m2 per minute. Serum glucose will be measured every 30 minutes for the first 150 minutes and then every 10 minutes during the last half hour of the test. The last 4 serum glucose measurements will averaged and recorded in mg/dl and will constitute the subject’s steady state plasma glucose (or SSPG). The SSPG provides a direct measure of insulin-mediated glucose uptake and will be used to describe each subject’s insulin sensitivity (33,34).

**Anthropometrics:** BMI, waist circumference and WHR will be measured at baseline and at weeks 8, 16, 32 and 40.

**IGF-1 levels:** Serum insulin like growth factor 1, or IGF 1, is a marker of GH status in the body. IGF 1 levels will be drawn at baseline and again at weeks 8, 16 and 32 and will be used along with clinical symptoms to assess rhGH dose adequacy. IGF 1 values greater than 2 standard deviations above the adult reference mean will result in a 50% rhGH dose reduction.

**Liver function tests, fasting glucose, hemoglobin (Hgb) A1C:** LFTs will be obtained at baseline and again at weeks 8, 16, 24, 32 and 40. Fasting glucose levels will be measured at baseline and at weeks 4, 8, 12, 16, 20, 24, 32 and 40. A HgbA1C will be used to measure each subject’s long-term glucose control and will be obtained at baseline and at weeks 8, 16 and 40.

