Serum glucose levels may transiently rise with rhGH due to its insulin antagonizing effects. It is expected that subjects in the combined pioglitazone/rhGH treatment group will be “protected” from this effect, whereas rhGH subjects *not* co-treated with a TZD may be susceptible. However, previous studies have shown that this susceptibility is reduced when moderate, rather than excessive, doses of rhGH are used (35). Marcus et. al showed that subjects with impaired glucose tolerance treated for 1 week with rhGH doses comparable to ours maintained similar glucose concentrations before and after treatment (37). In addition, Johannsson et. al showed that glycemic deterioration did not occur when rhGH doses similar to ours were used in people with underlying insulin resistance (25).

     The following measurements obtained on at least two separate occasions will be considered abnormal: (a) IGF-1 level greater than 2 standard deviations above the adult reference mean; OR (b) fasting glucose >126 mg/dl or random glucose > 200 mg/dl *plus* symptoms (ie: polyuria, polydipsia, ketosis) according to the revised ADA definition of diabetes mellitus. These abnormalities will result in the changes/interventions listed in *APPENDIX A* (please see *Page 13)*. *In order to maintain the study blind, a third-party investigator will be responsible for all drug dose adjustments during this study*.

The development of mild-to-moderate peripheral edema or symptoms indicative of rhGH-induced fluid retention (such as carpal tunnel syndrome, arthralgias, paresthesias) will also result in rhGH and/or TZD dose adjustments according to the algorithm in *APPENDIX B* (please see *Page 14*). In addition, the development of very severe or clinically life-threatening edema (ie: frank pulmonary edema, congestive heart failure) at any time during the study will result in prompt subject discontinuation.

*Thiazolidinediones (TZDs)*: TZDs can elevate liver function tests such as SGOT or SGPT. However, this is rarely clinically significant. Subjects will be discontinued from the study if LFTs are more than 2.5 times the upper normal range. In uncontrolled diabetics, weight gain may occur with TZDs as glucose levels fall. When serum glucose falls, glycosuria or excess glucose spillage in the urine ceases, and glucose is taken up into tissues. This often results in weight gain. Unlike uncontrolled diabetics, significant glycosuria does not usually

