occur in IGT patients. Therefore, TZD-induced weight gain is expected to be minimal in our study. In addition, TZDs can infrequently cause peripheral edema that is usually mild. *Table 3* summarizes the side effects that may occur with TZDs, according to Foyt, et. al, 2000 (38,39,40).

Table 3 (Adapted from Thiazolidinediones. Diabetes Mellitus: a Fundamental and Clinical Text. Lippincott Williams and Wilkins:788-797, 2000):

1. LFT increase  0.2% incidence of ALT > 3X upper limit of normal (placebo

= 0.2%)

2. Anemia  Hemoglobin decreases 0.64 g/dL; hematocrit decreases 2%

3. Edema  4.8% vs. placebo = 1.3%

4. Cardiac function  No change in LV mass or function; no data on stroke volume

5. Weight gain  1.2 kg with 4 mg dose; 3.5 kg with 8 mg dose; 2.3 kg with 8

(mean) mg dose + metformin; not reported for 4 mg dose + sulfonylurea

Subjects will be weighed at each P.E. visit and examined very carefully for peripheral edema. The development of mild-to-moderate peripheral edema during the treatment period will result in pioglitazone and/or rhGH dose adjustments according to the algorithm in *APPENDIX A* (please see pages 13 and 14). In addition, the development of very severe or clinically life-threatening edema (ie: frank pulmonary edema, congestive heart failure) at any time during the study will result in prompt subject discontinuation.

    Subjects will be instructed to report side effects that develop during the study by calling the Clinical Studies Unit or by appearing for an unscheduled evaluation.

2. **Alternative Approaches**

Estrogen-treated subjects: Oral estrogen can sometimes antagonize the action of GH at the GH receptor level. This results in lower IGF 1 levels despite normal or even high levels of GH (41,42,43). Adult GHD women taking oral estrogen can require twice as much rhGH as adult GHD men because IGF 1 levels may be 50% lower in the estrogen-treated women.

      An alternative approach is to use a higher rhGH dose in estrogen-treated subjects. However, subjects in this study are non-GHD adults, and higher doses of rhGH may produce unacceptable side effects and abnormally high IGF 1 levels. Therefore, subjects will receive the same starting dose and groups will be matched for menopausal status and estrogen use.

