# APPENDIX B: RhGH Dose Adjustment for IGF-1 > 2 SD Above Lab Reference Mean

1. **For subjects receiving *RhGH* 6-8 mcg/kg/day**, reduce *RhGH* dose by 2 mcg/kg/day. Repeat IGF-1 in 4 weeks. If IGF-1 level is within normal range, continue current *RhGH* dose. If IGF-1 level is still elevated

(>2 SD), go back to *APPENDIX B*.

B. **For subjects already dose-reduced to *RhGH* 4 mcg/kg/day**, discontinue from study.

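### The rhGH dose rule for a high IGF-1 is stated in two incompatible ways: a halving in Study Endpoints, a 2 mcg/kg/day step with later withdrawal in Appendix B

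*Protocol*

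**What the plan says.** The starting dose is in Experimental Design, Study drugs: "RhGH-treated subjects will begin self-injecting rhGH 8 mcg/kg SQ every day at week 5". Four places then bear on what happens when IGF-1 is high.

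- **Study Endpoints, IGF-1 levels.** "IGF 1 levels will be drawn at baseline and again at weeks 8, 16 and 32", and "IGF 1 values greater than 2 standard deviations above the adult reference mean will result in a 50% rhGH dose reduction". No confirmation, lower dose limit or withdrawal condition is stated.
- **Appendix B**, whose title is the rhGH adjustment for IGF-1 above 2 SD. For a subject on 6 to 8 mcg/kg/day the rhGH is reduced: "dose by 2 mcg/kg/day. Repeat IGF-1 in 4 weeks". A normal repeat keeps the subject on the reduced dose, and a high one sends the reader back through the same appendix. A subject already brought down to 4 mcg/kg/day leaves the study.
- **Drug side effects, rhGH.** "The following measurements obtained on at least two separate occasions will be considered abnormal: (a) IGF-1 level greater than 2 standard deviations" above the reference mean, or a glucose criterion. The action is said to be in Appendix A. Mild-to-moderate edema and fluid-retention symptoms are sent to Appendix B. A third-party investigator makes all dose changes to protect the blind.
- **Drug side effects, thiazolidinediones.** Mild-to-moderate edema is sent to Appendix A.

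**The concern.** Both actions are worded as instructions for the same marker at the same threshold, and neither is marked as a summary of the other or as subordinate to it. The third-party investigator has only the written rule to go on and cannot follow both.

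Two things are at stake. The first is rhGH exposure in the two groups that receive active rhGH, groups 2 and 4, with 15 subjects each. The second is retention. Appendix B ends in removal from the study rather than only from the drug, while Study Endpoints has no exit at all. A subject who leaves early may have no week 40 CT or week 43 insulin sensitivity test. The sample size statement needs 15 per group for insulin sensitivity and enrols exactly 15, so a single loss from an rhGH group would leave 14.

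**Working it through.** The protocol has no figure to reproduce here, so each rule is applied to the stated doses.

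**Inputs.** Start at 8 mcg/kg/day from week 5 (Study drugs). Rule S (Study Endpoints): new dose = 0.5 × current dose. Rule B (Appendix B): new dose = current dose − 2 at 6 to 8 mcg/kg/day, and withdrawal at 4. IGF-1 is scheduled at baseline and weeks 8, 16 and 32 (Study Endpoints).

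**Action at each dose when IGF-1 is above 2 SD**

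| Current dose (mcg/kg/day) | Rule S | Rule B |
|---|---|---|
| 8 | 0.5 × 8 = 4 (50% cut) | 8 − 2 = 6 (25% cut) |
| 6 | 0.5 × 6 = 3 (50% cut) | 6 − 2 = 4 (33% cut) |
| 4 | 0.5 × 4 = 2 (50% cut) | leaves the study |

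The rules agree in no row. After the first action from 8, the doses differ by 6 − 4 = 2 mcg/kg/day, which is 2/8 = 25% of the starting dose.

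**Successive high values from 8, each rule taken alone**

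- Rule S: 8, 4, 2, 1, with no withdrawal.
- Rule B: 8, 6, 4, then out of the study at the third high value.

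Appendix B as printed has no instruction for 3 or 2 mcg/kg/day, so doses reached by halving can fall outside it.

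**Timing**

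- Rule S, read as acting on any high value, can act at week 8.
- Rule B with its 4-week repeats takes a persistently high subject to 6 at week 8, to 4 at week 12, and out at week 16.
- If two on-treatment readings are needed first, as the rhGH side-effects text requires, and only scheduled draws are used, the earliest action is at week 16. That is 16 − 8 = 8 weeks later than acting on the week 8 value.

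**Appendix references**

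| Finding | Where the text sends it | Subject of the printed Appendix B |
|---|---|---|
| High IGF-1 | Appendix A (rhGH side effects) | High IGF-1 |
| Mild-to-moderate edema | Appendix B (rhGH side effects); Appendix A (thiazolidinedione side effects) | Not edema |

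**The case against.** The best attempt to reconcile the two rules is that Appendix B's two steps, 8 to 6 to 4, add up to a 50% reduction, so Study Endpoints might be summarising the whole sequence. The wording does not allow this. It ties the 50% cut to the IGF-1 value itself and does not describe a cap reached in stages. It can also be said that Study drugs points to the dose-adjustment pages, which suggests the appendix is the working rule, and that a single third-party investigator limits inconsistency between staff. Both points are fair, but neither tells that investigator which rule to apply.

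Several stronger readings are tempting and are not supported.

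- **Withdrawal at the second high reading under Study Endpoints (8 to 4 to out).** That text has no withdrawal rule. The path combines its halving with Appendix B's exit.
- **A 50% difference in dose.** This holds only with 4 as the base. Equally, 4 is 33% below 6.
- **The conflict drives missing outcomes in the rhGH arms.** The protocol gives no frequency of IGF-1 above 2 SD, and it describes the dosage as generally well tolerated. Only a possible effect on withdrawals can be claimed.
- **Flatly contradictory triggers.** Study Endpoints and the first step of Appendix B are silent on confirmation, so the two-reading definition could be read into both. This is an ambiguity, less serious than the conflict over the size of the cut.
- **A missing edema algorithm.** Appendix A is not in the text available for review. Its absence is not counted as an error and its content cannot be checked. What remains is a mismatch of labels.

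**Conclusion.** The two rules for a high IGF-1 are incompatible as written. From 8, 6 and 4 mcg/kg/day they give 4 against 6, 3 against 4, and 2 against withdrawal. This is an internal inconsistency in a safety-driven dosing rule and should be corrected. It rests only on the stated starting dose and the two printed instructions, and does not depend on what Appendix A contains.

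Exposure and possible withdrawals in groups 2 and 4 depend on which text is followed. The number of subjects affected cannot be derived from the protocol. The confirmation requirement and the appendix references are secondary clarifications. The 8-week delay assumes that two on-treatment readings are required and that no unscheduled draws are made.

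**What to change.** The sponsor should reconcile the IGF-1 paragraph of Study Endpoints, the rhGH and thiazolidinedione parts of Drug side effects, and Appendix B, so that the protocol states:

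- one dose reduction for a high IGF-1;
- one trigger, saying whether a single reading suffices or a second must confirm it, and when any repeat is drawn;
- one withdrawal condition, or a statement that there is none;
- one consistent appendix reference each for IGF-1, glucose and edema.

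Which rule holds is for the clinical team, and this review takes no view on it. The cost is a short protocol correction, with no change to sample size or analysis.

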## TENTATIVE SEQUENCE FOR INVESTIGATION

***Baseline*                        *Week #***

Test/event     (-4 to 0)  4      8   12     16    20 24     32     40 43

Physical exam        x      x          x     x           x     x x        x      x x

Anthropometrics       x               x                x        x x

CT abdomen            x                                                               x

OGTT                                                                x

IST                x                                                                x

IGF 1                 x                x x                x

LFTs                 x             x                      x         x x       x

Glucose               x    x     x        x        x       x     x      x x

Hgb A1C               x             x                       x          x

H. **POTENTIAL EXPERIMENTAL DIFFICULTIES AND ALTERNATIVE APPROACHES**

1. **Drug side effects**

*Recombinant human growth hormone (rhGH):* Side effects of rhGH include arthralgias and carpal tunnel symptoms (pain and paresthesias in the anterior wrist, palm and digits). These side effects are generally mild

and disappear either spontaneously or with rhGH dose reduction. Fluid retention may also occur in GHD patients and, less commonly, in non-GHD patients. In GHD patients, this is due to a dose-dependent

normalization of tissue hydration with GHD replacement (35). In non-GHD patients, fluid retention is generally mild and resolves spontaneously or with dose reduction. *Table 2* lists side effects attributed to rhGH in GH-deficient adults according to KIMS, a large pharmacoepidemiological survey(36):

Table 2 (from GH Replacement in Adults: the first 5 years of KIMS. Oxford PharmaGenesisTM Ltd:182-189, 2000):

[figure not shown]

Serum glucose levels may transiently rise with rhGH due to its insulin antagonizing effects. It is expected that subjects in the combined pioglitazone/rhGH treatment group will be “protected” from this effect, whereas rhGH subjects *not* co-treated with a TZD may be susceptible. However, previous studies have shown that this susceptibility is reduced when moderate, rather than excessive, doses of rhGH are used (35). Marcus et. al showed that subjects with impaired glucose tolerance treated for 1 week with rhGH doses comparable to ours maintained similar glucose concentrations before and after treatment (37). In addition, Johannsson et. al showed that glycemic deterioration did not occur when rhGH doses similar to ours were used in people with underlying insulin resistance (25).

     The following measurements obtained on at least two separate occasions will be considered abnormal: (a) IGF-1 level greater than 2 standard deviations above the adult reference mean; OR (b) fasting glucose >126 mg/dl or random glucose > 200 mg/dl *plus* symptoms (ie: polyuria, polydipsia, ketosis) according to the revised ADA definition of diabetes mellitus. These abnormalities will result in the changes/interventions listed in *APPENDIX A* (please see *Page 13)*. *In order to maintain the study blind, a third-party investigator will be responsible for all drug dose adjustments during this study*.

The development of mild-to-moderate peripheral edema or symptoms indicative of rhGH-induced fluid retention (such as carpal tunnel syndrome, arthralgias, paresthesias) will also result in rhGH and/or TZD dose adjustments according to the algorithm in *APPENDIX B* (please see *Page 14*). In addition, the development of very severe or clinically life-threatening edema (ie: frank pulmonary edema, congestive heart failure) at any time during the study will result in prompt subject discontinuation.

*Thiazolidinediones (TZDs)*: TZDs can elevate liver function tests such as SGOT or SGPT. However, this is rarely clinically significant. Subjects will be discontinued from the study if LFTs are more than 2.5 times the upper normal range. In uncontrolled diabetics, weight gain may occur with TZDs as glucose levels fall. When serum glucose falls, glycosuria or excess glucose spillage in the urine ceases, and glucose is taken up into tissues. This often results in weight gain. Unlike uncontrolled diabetics, significant glycosuria does not usually

occur in IGT patients. Therefore, TZD-induced weight gain is expected to be minimal in our study. In addition, TZDs can infrequently cause peripheral edema that is usually mild. *Table 3* summarizes the side effects that may occur with TZDs, according to Foyt, et. al, 2000 (38,39,40).

Table 3 (Adapted from Thiazolidinediones. Diabetes Mellitus: a Fundamental and Clinical Text. Lippincott Williams and Wilkins:788-797, 2000):

1. LFT increase  0.2% incidence of ALT > 3X upper limit of normal (placebo

= 0.2%)

2. Anemia  Hemoglobin decreases 0.64 g/dL; hematocrit decreases 2%

3. Edema  4.8% vs. placebo = 1.3%

4. Cardiac function  No change in LV mass or function; no data on stroke volume

5. Weight gain  1.2 kg with 4 mg dose; 3.5 kg with 8 mg dose; 2.3 kg with 8

(mean) mg dose + metformin; not reported for 4 mg dose + sulfonylurea

Subjects will be weighed at each P.E. visit and examined very carefully for peripheral edema. The development of mild-to-moderate peripheral edema during the treatment period will result in pioglitazone and/or rhGH dose adjustments according to the algorithm in *APPENDIX A* (please see pages 13 and 14). In addition, the development of very severe or clinically life-threatening edema (ie: frank pulmonary edema, congestive heart failure) at any time during the study will result in prompt subject discontinuation.

    Subjects will be instructed to report side effects that develop during the study by calling the Clinical Studies Unit or by appearing for an unscheduled evaluation.

2. **Alternative Approaches**

Estrogen-treated subjects: Oral estrogen can sometimes antagonize the action of GH at the GH receptor level. This results in lower IGF 1 levels despite normal or even high levels of GH (41,42,43). Adult GHD women taking oral estrogen can require twice as much rhGH as adult GHD men because IGF 1 levels may be 50% lower in the estrogen-treated women.

      An alternative approach is to use a higher rhGH dose in estrogen-treated subjects. However, subjects in this study are non-GHD adults, and higher doses of rhGH may produce unacceptable side effects and abnormally high IGF 1 levels. Therefore, subjects will receive the same starting dose and groups will be matched for menopausal status and estrogen use.

TZDs versus diet plus exercise: An alternative approach that might obviate the need for insulin sensitizer therapy is diet and exercise. However, this approach will not be used in this study for two reasons. First, many

viscerally obese, IGT adults have already tried diet and exercise and failed. Secondly, previous studies have shown that diet and exercise cannot overcome the transient insulin resistance and hyperinsulinemia associated with rhGH (44,45).

E. **METHODS OF DATA ANALYSIS**

   Data will be analyzed using StatView software for Microsoft Windows (SAS Institute Inc., Cary, NC). All data will be expressed as the mean +/- SE. A Student’s *t* test will be used to compare baseline values of the subject groups. For measurements pertaining to visceral fat, insulin sensitivity and glucose metabolism, ANOVAs for repeated measures will be used to analyze differences between data obtained at all time points. Area under the curve (AUC) for glucose data will be determined using the trapezoid method. In addition, results will be considered significant at *P* < 0.05.

F. **SIGNIFICANCE**

A. **Prevention of type 2 diabetes** **in viscerally obese adults with IGT**

The growing health care burden of type 2 diabetes mellitus in the U.S. demands that newer, more effective diabetes prevention strategies be implemented. One way to achieve diabetes prevention is to target adults who are at greatest risk for developing diabetes, such as viscerally obese adults with IGT.

Recent studies like the Diabetes Prevention Program (DPP) Trial indicate that, in individuals with IGT, interventions that result in visceral fat reduction also significantly reduce the risk of developing overt diabetes. Unfortunately, in non-experimental settings, many obese individuals have had little success in achieving visceral fat reduction with current weight loss modalities such as diet, exercise or anorexogenic drugs. This lack of success is often related to noncompliance and recidivism with diet and exercise and with limited overall benefit, intolerable side effects and/or addictive potential with anorexogenic medications. Furthermore, the potent weight-reducing effects of bariatric surgery are often eclipsed by severe gastrointestinal complications postoperatively and, in rare circumstances, an increase in mortality.

Unlike these options, both pioglitazone and rhGH are generally well tolerated and are effective in promoting visceral fat loss. Furthermore, the combined use of both drugs over a long-term period might have a greater (ie: additive or synergistic) effect in reducing visceral fat and improving insulin sensitivity compared with the use of either drug alone. It is anticipated that pioglitazone plus prolonged rhGH administration will help to prevent diabetes mellitus in viscerally obese adults with IGT, in part through visceral fat reduction. If this is prospectively shown to occur, then the long-term savings in health care dollars with diabetes prevention would offset the short-term cost of either pioglitazone or growth hormone.

B. **Prevention of rhGH-induced insulin resistance during the first 6 weeks of therapy**

Many individuals who might otherwise benefit from the lipolytic and insulin sensitizing effects of rhGH go untreated because they have underlying (ie: pre-existing) insulin resistance. This includes the following patient populations:

 Viscerally obese adults with IGT

 Insulin-resistant adults with growth hormone deficiency (GHD)

 Adults with hereditary or acquired lipodystrophy syndromes (ie: HIV (+) patients on protease inhibitors)

 Women with PCOS and insulin resistance

 Viscerally obese adults with type 2 diabetes and a normal BMI (ie: people from the Indian subcontinent)

RhGH treatment is often withheld in these groups because of concerns about short-term adverse effects on insulin action and glucose metabolism. However, the combination of a TZD and rhGH is expected to prevent or minimize any short-term worsening in insulin resistance in such individuals and thus allow treatment to continue. Therefore, the aforementioned groups are potential candidates for this combination therapy in the future.

C. **Improvement in Insulin Sensitivity in Adults with Growth Hormone Deficiency (GHD)**

RhGH is FDA-approved for replacement in adults with documented growth hormone deficiency, or GHD. By definition, GHD adults have inadequate growth hormone production and secretion due to pituitary/hypothalamic injury (ie: from a large tumor, prior radiation treatment or brain trauma). GHD adults typically have an abnormal body composition, including diminished lean body mass and increased body fat. In addition, death due to cardiovascular disease is common in this population, and it is believed that both visceral obesity and insulin resistance contribute to the increase in cardiovascular mortality. Compared with the use of rhGH alone, it is possible that rhGH plus pioglitazone might help to optimize body composition and insulin sensitivity in GHD adults and, therefore, reduce their cardiovascular risk. It is also possible that the frequent untoward occurrence of transient insulin resistance during the first 6 weeks of rhGH replacement in GHD adults might be prevented by co-treatment with pioglitazone.

D. **Reduction in CV Disease Risk Associated with Visceral Obesity and Insulin Resistance**

Loss of visceral fat helps to reduce cardiovascular (CV) risk indirectly by improving the metabolic abnormalities associated with visceral fat excess: dyslipidemia, hypertension, insulin resistance and hyperglycemia. TZDs and rhGH have been independently shown to effectively reduce visceral fat in insulin-

resistant, abdominally obese adults and ameliorate metabolic variables such as hyperlipidemia and insulin resistance that are associated with visceral adiposity. It is possible that the combined use of a TZD with rhGH will result in an even greater reduction in visceral fat and insulin resistance compared with the use of either drug alone, and this in turn might lead to a reduction in cardiovascular morbidity and mortality.

While rhGH and TZDs share in common the ability to reduce visceral fat and increase insulin sensitivity, each drug also acts in a different manner to potentially improve cardiovascular outcome. In viscerally obese growth hormone deficient (GHD) adults, for example, rhGH has been shown to significantly reduce carotid artery intima-media thickness and improve brachial artery blood flow. After 3-6 months of rhGH administration, the carotid artery intima-media thickness of adult GHD men as measured by ultrasound becomes very similar to that of healthy age- and sex-matched controls (46). These data suggest a possible therapeutic role for rhGH in reducing long-term cardiovascular disease and stroke risk by *directly* improving vascular morphology and function. Similarly, TZDs have been shown to yield a multitude of benefits on cardiovascular risk factors that might be unrelated to changes in insulin sensitivity or glucose metabolism. These include improvements in cardiovascular markers such as C-reactive protein (CRP), interleukin-6, and PAI-1, and a reduction in fibrinogen levels, platelet aggregation and dyslipidemia (27). In addition, TZDs may have direct cardiovascular benefits that include decreasing intima-media thickness, reducing neovascularization after coronary vessel injury and improving arterial blood flow (27). Therefore, both TZDs and rhGH appear to have direct and indirect beneficial long-term effects on the cardiovascular system, and many of these benefits are mediated by a reduction in visceral fat and an improvement in insulin sensitivity. It is expected that the long-term combined use of rhGH and pioglitazone in viscerally obese, insulin resistant adults will help to reduce cardiovascular risk factors and cardiovascular disease.

G. **REFERENCES *(for Protocol only)***

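### The protocol sends mild-to-moderate edema to Appendix B in one place and to Appendix A in another, and Appendix B as printed is the IGF-1 rule

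*Protocol*

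**What the plan says.** All the references at issue are in the current Protocol text.

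- **Section H.1, rhGH text, laboratory triggers.** IGF-1 above 2 SD, or diabetic-range glucose, on at least two occasions counts as abnormal. "These abnormalities will result in the changes/interventions listed in" Appendix A, placed on page 13.
- **Section H.1, rhGH text, edema and symptoms.** Appendix B, placed on page 14, is the target for mild-to-moderate peripheral edema and for symptoms that point to fluid retention from rhGH. The wording, "such as carpal tunnel syndrome, arthralgias, paresthesias) will also result in rhGH and/or TZD dose adjustments according to the algorithm in", covers both drugs.
- **Section H.1, Thiazolidinediones text, edema.** Appendix A is the target. The sentence, "The development of mild-to-moderate peripheral edema during the treatment period will result in pioglitazone and/or rhGH dose adjustments according to the algorithm in", carries the page note "please see pages 13 and 14".
- **Appendix B.** It is headed "APPENDIX B: RhGH Dose Adjustment for IGF-1 > 2 SD Above Lab Reference Mean". For subjects on 6 to 8 mcg/kg/day it lowers the rhGH "dose by 2 mcg/kg/day. Repeat IGF-1 in 4 weeks. If IGF-1 level is within normal range, continue current" that dose. If IGF-1 stays high the reader returns to Appendix B, and subjects already at 4 mcg/kg/day leave the study.
- **Who acts.** To protect the blind, "a third-party investigator will be responsible for all drug dose adjustments during this study".

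**The concern.** These are working safety instructions, to be carried out by a third party outside the blinded team. Two sentences in one section name the same event, the same severity and the same two drugs, yet cite different appendices.

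Someone who follows the rhGH text literally for edema arrives at a rule for a different trigger. As printed, that rule changes only rhGH and rechecks only IGF-1. The gap is plainest in group 3 (pioglitazone plus injected placebo): the printed rule offers no step on the active drug, although the Thiazolidinediones text lists edema as a TZD effect and the Study drugs section foresees a change of pioglitazone dose for it. At stake is whether mild-to-moderate edema and fluid-retention symptoms are handled by the intended rule, and in the same way for every subject.

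**Working it through.** The protocol gives no figure on this point, so the check sets the references side by side.

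| Trigger | H.1, rhGH text | H.1, Thiazolidinediones text | Appendix B as printed |
|---|---|---|---|
| Mild-to-moderate edema | Appendix B | Appendix A | No step shown |
| Fluid-retention symptoms | Appendix B | Not addressed | No step shown |
| IGF-1 above 2 SD | Appendix A | Not addressed | This is its subject |
| Diabetic-range glucose | Appendix A | Not addressed | No step shown |

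1. **Edema.** The first row is a direct contradiction between two current sentences, and it stands whatever Appendix A contains. If only Appendix A holds the edema algorithm, the rhGH text is wrong. If only Appendix B holds it, in text not shown here, the Thiazolidinediones text is wrong. If each appendix holds part of it, each sentence cites only part. In every case at least one reference needs correcting.

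2. **Is the Appendix B label a stray heading?** Probably not. The body matches the heading: the trigger, the recheck and the loop back are all about IGF-1, and the loop names Appendix B itself.

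3. **IGF-1.** The rhGH text sends this trigger to Appendix A, but the rule for it is printed under Appendix B. Exchanging the two letters in the rhGH text would send IGF-1 to the printed IGF-1 rule and edema to the appendix that the Thiazolidinediones text already names. One swap therefore accounts for both mismatches. This is an inference, because Appendix A cannot be read.

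4. **Glucose.** Its cited target is Appendix A, so nothing can be checked.

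5. **Severe edema.** Both parts of H.1 withdraw a subject with life-threatening edema. The conflict does not reach that case.

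**The case against.** The strongest reply is that little harm follows. The rhGH text places Appendix A on page 13 and Appendix B on page 14, so every reference leads to one or both of two pages. Appendix B's heading states its trigger, so a reader looking for an edema rule would see the mismatch at once. One third-party investigator handles all adjustments and could settle the matter once. This stands, and it is why the point is minor. It does not remove the contradiction, which leaves a dosing rule for the user to reconcile.

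Several stronger readings are tempting, but the documents do not support them:

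- **That the protocol has no edema algorithm.** Appendix A is not in the text at hand. The list labels in Appendix B (a numeral, then a letter) suggest formatting was lost, so its text may be incomplete. Absence cannot be concluded.
- **That the Study drugs section adds a third conflicting target.** It refers side effects of both drugs to pages 13 and 14, which by the rhGH text's own numbering covers both appendices. It conflicts with neither part of H.1.
- **That the Thiazolidinediones text gives the wrong pages for Appendix A.** The text at hand carries no page numbers, and Appendix A could run from page 13 onto page 14.
- **That the IGF-1 reference is proven wrong.** Appendix A could hold an IGF-1 step or refer onward to Appendix B. The mis-reference is probable only.
- **That Table 3's edema rates ("4.8% vs. placebo = 1.3"%) measure the harm.** They bear on how often edema occurs, not how often a wrong dose follows. That table's weight line also refers to 4 mg and 8 mg doses, not this trial's 15 mg and 30 mg.

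**Conclusion.** The point holds as an internal contradiction of minor severity. It is certain that the two parts of section H.1 cite different appendices for the same mild-to-moderate edema, and that Appendix B as shown is an IGF-1 rule for rhGH alone. It is probable, not certain, that the rhGH text has exchanged the two appendices and so also misdirects IGF-1 above 2 SD.

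The effect is confined to safety dose adjustment for mild-to-moderate edema and fluid-retention symptoms, and probably for IGF-1. Endpoints, sample size and alpha are untouched. No count of affected subjects is offered, because the documents give no basis for how often the wrong rule would be applied. The edema conflict rests only on the two sentences in H.1. The swap rests on Appendix B's printed text being representative of the whole appendix.

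**What to change.** First check both references once against the full appendices. Then:

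- in section H.1, make the rhGH text and the Thiazolidinediones text name the same appendix for mild-to-moderate edema and fluid-retention symptoms, namely Appendix A if it holds that algorithm for both drugs;
- in the rhGH text, point IGF-1 above 2 SD to Appendix B.

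The Study drugs section needs no change. The cost is a few corrected references and one check, with no added visits, staff or tests.

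A separate matter is best settled in the same edit. The IGF-1 paragraph under Study Endpoints calls for a 50% rhGH reduction above 2 SD. Appendix B's step of 2 mcg/kg/day is 2/8 = 25% from 8 mcg/kg and 2/6 = 33% from 6 mcg/kg. Correcting the reference alone would not reconcile those two rules.
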